## Methods

### Study design

The study will test optimized implementation strategies informed by behavioral economics in a six-arm factorial hybrid type 3 cluster implementation RCT testing the effectiveness of nudges to clinicians (to either refer to a genetics clinic or order genetic testing), nudges to patients (to discuss genetic testing with their clinician), nudges to both, or neither (Fig. 2). The two versions of the clinician nudge will help to test the effects of a local adaptation to this implementation strategy.

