**Fig. 4 Fig4:**
[figure not shown]
PennChart Genomics Initiative website. Publicly available link: https://www.med.upenn.edu/pgi/

Moderators of effectiveness will be investigated through analyzing associations with variables available via EHR for patients (e.g., race) and clinicians (e.g., location of practice). Tracking referrals and genetic test orders in the EHR will allow for comparisons in uptake across clinics and patient groups.

The primary implementation outcome will be the time to genetic testing within six months of the patient’s initial visit with a randomized clinician. Each of the six randomization groups, as detailed in Fig. 2, will be analyzed separately.

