#### Sample size, power, and statistical analysis

Based on preliminary data, up to 3800 patients are anticipated to be available to include in the study (based on prior assessment of eligible patients over the past three years), interacting with approximately 230 clinicians represented by approximately 100 clinician clusters. Clinician nudge assignment will be randomized by clinician cluster, while patient nudges will be assigned independently. This independent randomization makes the main effect for patient nudges a within-cluster comparison. The analysis will use the time to genetic testing outcome registered in the EHR within six months after the visit when the nudges were delivered. The exchangeable correlation (for our clustered data) observed from other studies is small (0.07). Our goal is to achieve at least 80% power using a two-sided type-1 error of 5%. Based on prior data, our outcome is expected to be 10% in the absence of intervention by the 6-month censoring time. We anticipate that the patient nudge will increase testing by 5% (HR=1.54), and clinician nudges will increase testing by 10% (HR=2.12). In addition, the two nudges together may increase testing more than the strict additive main effects and add up to an additional 10% testing (25% total increase). We calculated power by simulating random data sets in Stata 18. We assumed an exponential daily hazard with event times correlated within cluster and fitted those data sets with aCox regression model. Model variances were corrected using cluster-correlation. Our design yields more than 95% power for the patient and provider nudges regardless of correlation. It also provides at least 90% power to detect (within-between) interactions. Power remains above 80% for a wide variety of departures from our original assumptions. Power for the main effect of provider nudges may drop below 80% for high within-subject correlations (above 0.2), and overall power to detect all differences is reduced as the baseline hazard increases (beyond 20% testing by 6 months).

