Time to event outcomes (incidence of testing, incidence of ordering, incidence of referring, incidence of clinician action) will be analyzed using Cox regression, censoring at the six-month end of observation. The study design is factorial, and models will contain categorical predictor terms for clinician (refer vs. order vs. control) and/or patient nudge vs. control. We will include adjustments for fixed effects of site. We will control for type 1 error inflation by hierarchical testing, starting with the overall model significance, followed by overall effects of clinician nudges and then patient nudges. Once we have fitted the main effects model, we will test for interaction between clinician and patient nudges and retain that interaction term if significant (alpha=5%). We will test the two clinician nudges separately and combine them if there are no significant differences, and use a similar approach for other study outcomes using GLM (or GEE for repeated measures) using the appropriate distribution family.

While our design is factorial, with the presumption that a patient will remain in one clinician cluster, we recognize that there will be some movement or crossover between clinician clusters and treatments. For that reason, our primary analysis will censor patient observations at the point of crossover. We will also conduct a secondary analysis “as treated”, using time-varying covariates to represent the accumulated clinician nudge exposures over time.

Next, we will examine variability in our outcomes by treatment arm and moderators (patient-, clinician-, and system-level) using interaction terms within the regression. We will fit an adjusted model using the same approach described in the primary analysis. Moderators of particular interest will be patient-level (e.g., diagnosis, race, geocoded indicator of socio-economic status), clinician-level (e.g., years in practice), and system-level data (e.g., community vs. hospital-based). If there are no interactions with the two clinician nudge arms, they will be combined in subsequent moderator analysis following the same approach described above.

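### Order and Refer are combined whenever they do not differ significantly, so a test with limited power chooses which clinician effect is reported; the six-group sentence in Study design also conflicts with the factorial model

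*Protocol article*

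**What the plan says.** All references are to the protocol article.

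- **Sample size, power, and statistical analysis**, on the clinician arms: "We will test the two clinician nudges separately and combine them if there are no significant differences". Other outcomes follow a similar approach, so the rule applies first to the primary outcome, time to genetic testing.
- The same section, on moderators: "If there are no interactions with the two clinician nudge arms, they will be combined in subsequent moderator analysis".
- The same section describes a Cox model with a three-level clinician factor and a patient-nudge factor. An interaction term is kept only if significant at 5%. The testing order is overall model, overall clinician effect, then patient effect. The combining rule is stated after this order.
- **Study design**, opening paragraph, on why there are two clinician nudges: "The two versions of the clinician nudge will help to test the effects of a local adaptation to this implementation strategy".
- **Study design**, after Fig. 4, directly after the primary outcome is named: "Each of the six randomization groups, as detailed in Fig. 2, will be analyzed separately".

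The power statement covers one common clinician effect (10% rising to 20%, HR 2.12) and the patient nudge (10% rising to 15%, HR 1.54). It gives neither an expected Order–Refer difference nor power to detect one.

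**The concern.** Order and Refer ask clinicians to do different things: place the test order themselves, or send the patient to a genetics clinic. A health system choosing between them needs an estimate for each. Under the rule, a non-significant difference replaces the two estimates by one average, with no margin or equivalence criterion to justify calling them equal. Because the choice is made on the same data, the usual standard errors ignore it.

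Two things can go wrong. If both nudges work to different degrees, each interval is centred on the average too often and covers its own true effect less often than stated. If only one works, the other can share its credit. The moderator rule has the same logic, with the trigger being absence of interaction; no power is stated for those interaction tests either.

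The six-group sentence adds a conflict. A main-effects model with a conditional interaction and conditional combining does not analyse six groups separately, so the article gives two descriptions of the primary analysis.

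**Working it through.** **Inputs from the article.** Two-sided alpha 5% and target power of at least 80%; "up to 3800 patients are anticipated to be available to include in the study"; "approximately 230 clinicians represented by approximately 100 clinician clusters"; within-cluster correlation 0.07; control rate 10% by six months; +10 points for clinician nudges and +5 for the patient nudge.

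**Assumptions, because the article does not state them.** Clusters allocated 1:1:1 (about 33 clusters and 3800/3 = 1267 patients per clinician arm); equal clusters of 3800/100 = 38; no loss from censoring at crossover; Order and Refer rates centred on 20% unless stated.

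**Step 1: reproduce the stated figures.**
- HR = ln(1−p1)/ln(1−p0). Clinician: ln(0.80)/ln(0.90) = 2.118. Patient: ln(0.85)/ln(0.90) = 1.5425. Both agree with the article.
- Design effect = 1 + 37 × 0.07 = 3.59. Effective size per clinician arm = 1267/3.59 = 353.
- Both nudges together versus control, 20% vs 10%: SE = √(0.16/706 + 0.09/353) = 0.0219; z = 4.56; power = Φ(4.56 − 1.96) = 99.5%. Other methods (null-variance formula, Schoenfeld, simulation) give 99.1% to 99.8%. Patient nudge: 97% to 99.8%. The stated figure of more than 95% is reproduced at 0.07.

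**Step 2: power of the test that decides on combining.** SE = √[(pO(1−pO) + pR(1−pR))/353]; power = Φ(difference/SE − 1.96). The last column is a simulation of the factorial design with event times correlated within cluster and a cluster-robust constant-hazard model standing in for Cox.

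| Order vs Refer | SE | z | Power, formula | Power, simulation |
|---|---|---|---|---|
| 22% vs 18% | 0.0301 | 1.33 | 26% | 34% |
| 22.5% vs 17.5% | 0.0301 | 1.66 | 38% | 51% |
| 23% vs 17% | 0.0300 | 2.00 | 51% | 64% |
| 25% vs 15% | 0.0299 | 3.35 | 92% | 98.5% |

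At a correlation of 0.2 the 5-point figure falls to 19–28%.

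**Step 3: what the rule does.** Cluster-level simulation of six-month proportions (beta-binomial, correlation 0.07, 20,000 runs), control at 10%:
- *Order 22.5%, Refer 17.5%.* The true gains are 12.5 and 7.5 points; combined, both are reported as about 10. The arms are combined in about 63% of trials (the formula gives 100% − 38% = 62%). Nominal 95% intervals cover about 84% for Refer and 86% for Order; separate intervals cover 95%.
- *Order 15%, Refer 10% (no Refer effect).* The arms are combined in about 49% of trials. Refer is declared effective in about 14–15% of trials, or 12% if a significant two-degree-of-freedom overall test is required first. Separate tests give 5%.
- *All three at 10%.* The rate is about 5–6%, or 3% after the overall test: no material inflation.

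**Step 4: is combining needed for power?** Each nudge alone versus control, 20% vs 10%: SE = √[(0.16 + 0.09)/353] = 0.0266; z = 3.76; power = Φ(1.80) = 96%. It is not needed to reach 80%.

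**Step 5: the two descriptions of the analysis.** Study design has six groups, each analysed separately. The statistical section has main effects over the margins of the factorial, with at most an added interaction and possibly a two-level clinician factor. Both cannot be the primary analysis.

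**The case against.** **Does the rule choose the primary test?** A reader might infer this. The article does not support it: the hierarchy names an overall clinician effect before the combining step, and with a three-level factor that can be a fixed two-degree-of-freedom test. The rule then decides which clinician effect is estimated and reported. The article does not say whether overall means that test or a combined contrast, so the ambiguity remains. The patient-nudge test does not depend on the rule.

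**Does the six-group sentence cost the patient nudge its power?** Someone could compare patient nudge alone with neither nudge (about 633 per group) and find about 76%, or less with a Bonferroni correction. That is hypothetical. The sentence names no pairwise test, no such correction appears in the article, and the statistical section defines the patient effect as a within-cluster main effect. Only the conflict in wording stands.

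**Is limited power a matter of the difference chosen?** Partly. The article states no expected difference, and a 10-point difference would be found about 92% of the time. The allocation ratio and cluster sizes are also assumed. Reading 0.07 as a correlation of binary outcomes or of event times moves the figures, which is why ranges are given.

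**Might separate estimates be reported anyway?** They might: the article says the nudges are tested separately first, and the full analysis plan is not shown. But the combining rule itself is stated here, and it determines the main clinician result.

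**Conclusion.** The point holds as a fault in how the reported clinician effect is chosen, and as a conflict between two sections. For differences up to about 5 or 6 points, half or more of the assumed 10-point nudge effect, the deciding test has roughly 26–64% power, so a non-significant result is poor evidence that Order and Refer are equal. The consequences in the scenarios examined are interval coverage of about 84–86% instead of 95%, and a false claim for an ineffective Refer nudge in about 12–15% of trials instead of 5%. These figures rest on 1:1:1 allocation, equal clusters of 38, a correlation of 0.07 and no crossover censoring; unequal clusters or censoring would lower Order-versus-Refer power further. General inflation of the type 1 error and a weakened patient-nudge test are not shown. It should be corrected, but it does not undermine the design.

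**What to change.** 1. Delete both combining rules, for the main analysis and for the moderators.
2. State in advance what the overall clinician test is: either the two-degree-of-freedom test of the three-level factor, or the average of the two nudges versus control. Keep it whatever the Order-versus-Refer result.
3. Always report Order vs control, Refer vs control and Order vs Refer with confidence intervals. Place any of these meant as confirmatory claims in the existing hierarchy.
4. Reword the six-group sentence in Study design so that the factorial contrasts are primary and six-group results are descriptive.

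The cost is wording and a few more reported estimates from the same models. Each nudge's interval will be wider than a combined one: at 20% vs 10% the standard errors are 0.0266 and 0.0219, so half-widths are about 1.96 × 0.0266 = 5.2 points against 1.96 × 0.0219 = 4.3. With 96% power for each nudge against control under these assumptions, that is affordable.

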**Supplementary Information:**

The online version contains supplementary material available at 10.1186/s13012-024-01385-5.

Contributions to the literature
This paper describes the development of implementation strategies and electronic phenotyping to support an implementation clinical trial focused on genetic testing.This study will evaluate the use of implementation strategies informed by behavioral economics to promote uptake of genetic testing in a group of conditions for which the results may change medical management.This study may identify novel supports to reduce disparities and increase uptake of genetic testing in patients with pre-selected conditions.

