This study aims to refine clinician- and patient-directed implementation strategies informed by behavioral economics to evaluate the effect on uptake of genomic medicine. Electronic phenotyping algorithms [80] will first be defined to identify patients for whom genetic testing is recommended. Nudges will be designed to address clinician and patient heuristics that can influence decision-making within complex medical care. We will conduct a hybrid type 3 cluster-randomized controlled trial (RCT) to evaluate these optimized patient- and/or clinician-directed strategies for increasing the use of genetic testing in conditions for which the results inform medical management. Given ongoing awareness of health disparities in genomic medicine [81, 82], and the shift in focus of health equity in implementation science [83–85], impact of these strategies in racial minorities will be evaluated. Methods and resources developed in this trial will then be disseminated through Penn websites (Fig. 1) and public websites.

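### Race and socio-economic moderation of time to testing is specified only on the hazard-ratio scale, which does not show whether nudges narrow or widen the gap in testing rates

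*Protocol article*

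**What the plan says.** In the protocol article, the section on sample size, power and statistical analysis assigns Cox regression to the time-to-event outcomes, censored at six months. For moderators it continues: "we will examine variability in our outcomes by treatment arm and moderators (patient-, clinician-, and system-level) using interaction terms within the regression". Race and a geocoded socio-economic indicator are among the patient-level moderators of particular interest, and the adjusted model follows the primary approach. The section names no other moderator method for time to testing. Its GLM/GEE provision is for other outcomes.

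The equity aim appears in several places. The contributions statement says "This study may identify novel supports to reduce disparities and increase uptake of genetic testing in patients with pre-selected conditions". The Background says "impact of these strategies in racial minorities will be evaluated". Study design reports preliminary data showing that testing rates differ by race in the selected conditions, and adds that EHR tracking makes it possible to compare uptake between patient groups. No section defines disparity or gives a scale for it.

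The power assumptions are stated on both scales. The baseline is "our outcome is expected to be 10% in the absence of intervention by the 6-month censoring time", and the effects are that "the patient nudge will increase testing by 5% (HR=1.54), and clinician nudges will increase testing by 10% (HR=2.12") in percentage points and hazard ratios together.

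**The concern.** A Cox interaction asks whether the hazard ratio for the nudge is the same in both groups. A reader interested in disparity will usually also ask whether the difference in the proportion tested became smaller. When baseline rates are equal, the two questions have much the same answer. When they differ, which is the article's own premise, and the nudge works, the answers can part.

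Two situations matter:
- A null interaction may be read as the nudges having left disparities alone, although the gap in testing rates has grown.
- A larger hazard ratio in the lower-rate group may be read as narrowing, although the gap in points has not moved.

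Because the article does not fix the scale for statements about disparity, that choice could be made after the results are seen, and the two scales can support different messages.

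**Working it through.** **Inputs.** From the sample-size section: 10% tested by six months without a nudge; HR 1.54 for the patient nudge and 2.12 for the clinician nudge; exponential event times in the power simulation. Assumed, because the article does not give them: baseline rates by race. I use pairs around 10%, from 11/9 to 15/5, with 20/10 and 30/15 as higher-baseline checks.

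**Reproducing the stated hazard ratios.** Under proportional hazards, HR = ln(1 − p1) / ln(1 − p0).
- Patient nudge, 10% to 15%: ln 0.85 / ln 0.90 = 1.54.
- Clinician nudge, 10% to 20%: ln 0.80 / ln 0.90 = 2.12.

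Both agree with the article.

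**Same hazard ratio in both groups (Cox interaction exactly 1.0).** In each group p1 = 1 − (1 − p0)^HR. For 12% vs 6% with HR 2.12:
- 1 − 0.88^2.12 = 23.7%
- 1 − 0.94^2.12 = 12.3%
- The gap goes from 6.0 to 11.4 points (factor 1.91), and the uptake ratio from 2.00 to 1.93.

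| Assumed baselines | Gap, no nudge | Gap, patient nudge (HR 1.54) | Gap, clinician nudge (HR 2.12) |
|---|---|---|---|
| 11% vs 9% | 2.0 | 2.9 (×1.45) | 3.8 (×1.88) |
| 12% vs 8% | 4.0 | 5.8 (×1.45) | 7.5 (×1.88) |
| 12% vs 6% | 6.0 | 8.8 (×1.46) | 11.4 (×1.91) |
| 15% vs 5% | 10.0 | 14.5 (×1.45) | 18.8 (×1.88) |

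At higher baselines the clinician-nudge factor falls to 1.77 (20/10) and 1.59 (30/15), still above 1.

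**Same gain in points in both groups (gap unchanged).** With +10 points from 12% and 6%:
- Higher-rate group: ln 0.78 / ln 0.88 = 1.94.
- Lower-rate group: ln 0.84 / ln 0.94 = 2.82.
- Interaction HR: 2.82 / 1.94 = 1.45, although the gap is still 6.0 points.

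From 12% and 8% the interaction HR is 2.38 / 1.94 = 1.22.

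**How often the two scales would disagree.** I simulated 3,800 patients, two thirds with a clinician nudge, baselines 12/6, HR 2.12 in both groups, and a lower-rate group making up 20% to 40% of patients (2,000 runs each). A complementary log-log contrast at six months stood in for the Cox interaction. The ratio-scale test rejected in about 4% of runs, as it should when its null hypothesis is true. A test of the change in absolute gap rejected in about 60% to 72%. Clustering was ignored, so the second figure is probably optimistic.

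**The case against.** The strongest reply is that the article asks about moderation of effectiveness, and an interaction term in the primary model answers that coherently. The dependence of interaction on scale is a general property and no error of this trial. The planned models and data already contain what is needed for absolute contrasts, the full analysis plan is not shown and may specify them, and the contributions statement is hedged.

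Much of this stands. A reader might infer that disparity will be judged solely by the Cox interaction, or that a null interaction would be the wrong answer. The document supports neither inference. It never says that the interaction is the sole basis for statements about disparity, never defines disparity as an absolute difference, and sets no rule for declaring that there is no differential effect. On the relative scale a null result is right: with 12% vs 6%, the uptake ratio barely moves (2.00 to 1.93). Likewise, the interaction of 1.45 in the equal-gain case correctly reports a larger relative effect in the lower-rate group.

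What the reply does not remove is the mismatch within the stated text. The moderator method that is given works on one scale, the disparity premise is expressed in testing rates, and no sentence connects them. The remark in Study design about comparing uptake between patient groups concerns what the tracked data permit. It does not name a nudge-versus-control change in the gap, or a scale.

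**Conclusion.** The point holds as an improvement to a secondary analysis. The only moderator method stated for time to testing measures effect modification on the hazard-ratio scale, and by itself it does not show whether nudges narrow or widen the difference in testing rates.

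Under equal hazard ratios, the absolute gap would grow by a factor of about 1.9 for the clinician nudge and about 1.45 to 1.5 for the patient nudge. These sizes rest on proportional hazards, on the article's own hazard ratios, and on assumed baselines by race near the overall 10%. The widening persists, though smaller, at baselines up to 30/15. The factor near two belongs to the clinician nudge at low baselines and should not be quoted for the trial as a whole. The primary test and the sample size are not affected.

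**What to change.** Keep the Cox interaction and label it as effect modification on the ratio scale. For race and socio-economic status, add from the same fitted models:

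- the standardised six-month testing probability by group and nudge arm;
- the nudge-versus-control change in the absolute gap between groups, with a 95% confidence interval from a bootstrap that resamples clinician clusters.

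Report both scales, and state in advance that any claim of reduced or widened disparity names the scale it refers to. There is no need to make the absolute scale the sole basis for conclusions.

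The cost is some post-estimation code and a sentence or two of text, with no new data. The drawback is a second set of estimates, whose intervals may be wide.
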